## Abstract

**Background:**

The prognosis of ischemic heart failure (IHF) is worse than non-IHM. Improving the management of IHF remains an urgent demand. In recent years, Qishen Yiqi dripping pills (QSYQ), a type of Chinese herbal medicine (CHM), has been popular for IHF combined with standard western medicine. However, relevant scientific evidence from the real clinical practice still is insufficient. The prospective cohort study aims to assess the effectiveness and safety of QSYQ plus standard western medicine for IHF in the real clinical practice.

**Methods:**

It is a multicenter, prospective, observational cohort study. A total of 1200 patients with IHF recruited from 84 hospitals in China will be assigned to exposure group (patients with QSYQ treatment) or non-exposed group (patients without QSYQ treatment) mainly according to patients’ preference in real clinical situation. The primary outcomes include New York Heart Association (NYHA) cardiac functional classification and Minnesota Living with Heart Failure Questionnaire (MLHFQ). The secondary outcomes include composite outcomes (all-cause mortality, frequency of re-admission or emergency due to cardiovascular events), left ventricular ejection fraction and cardiothoracic ratio, symptoms and signs obtained by the 4 Tradiational Chinese Medicine (TCM) diagnostic methods. Assessments will be performed at baseline, 1st and 3rd month after enrollment.

**Discussion:**

It will provide new evidence on QSYQ for IHF in real clinical practice.

**Study registration:**

This study has been registered on the Chinese Clinical Trial Registry (No: ChiCTR-ONRC-14004407).

## Background

1

Heart failure (HF) has become a major public health problem associated with high prevalence, poor prognosis and huge economic burden despite recent improvements of its treatment.^[1]^ Ischemic heart failure (IHF) is the most common type of HF. The prognosis of patients with IHF is worse than those with other types of HF.^[2–4]^ Improving the management of IHF remains an urgent demand.

Chinese herbal medicine (CHM) is popular for treating patients with IHF combined with routine western medicine in China.^[5]^ Qishen Yiqi dripping pills (QSYQ) consisting of active ingredients from Huangqi, Danshen, Sanqi, and Jiangxiang and it is a type of CHMs produced by Tasly Pharmaceutical Co. Ltd and approved for ischemic heart disease by China State Food and Drug Administration in 2003. Experimental research suggests QSYQ could be beneficial for IHF through multiple mechanisms such as inhibiting platelet aggregation, enhancing cardiac function, reducing serum brain natriuretic peptide (BNP). preventing cardiac ventricular remodeling, and so on.^[6–12]^ A 2014 systematic review suggests QSYQ could improve the cardiac function in patients with IHF without severe side-effects.^[13]^ However, current evidence from randomized clinical trials (RCTs) still remains inconclusive due to poor methodological quality such as small sample size, single center, and so on,^[13]^ and the external authenticity is limited in view of patients’ preference for treatment in real clinical practice.^[14]^ In this prospective cohort study, we aim to assess the effectiveness and safety of the combination of QSYQ and routine western medication for IHF considering patients’ preference in the real world.

## Methods

2

### Study design

2.1

It is a multicenter, prospective, observational cohort study. A total of 1200 outpatients with IHF from 84 hospitals will in different regions of China are divided into 2 cohorts: exposure group (patients with QSYQ treatment) and non-exposed group (patients without QSYQ treatment). The choice for groups will be mainly made according to patients’ preference. Assessments will be performed at baseline, 1 and 3 months after enrollment. Outcome assessors and statisticians responsible for the final analysis will be blinded. The details of the flow diagram are shown in Figure 1.

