### Sample size

2.4

According to a previous study,^[17]^ we assume that the rate of cardiac function improvement is 22% of patients in QSYQ group and 15% in control group. The sample size is same in 2 groups. A total sample size of 1200 patients should be recruited with a power of 0.8, a 2-sided alpha of 0.05 and a dropout rate of 20% by PASS 2011 software.

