### Intervention

2.5

The patients will be divided into 2 cohorts: exposure group and non-exposed group according to whether are taking QSYQ in real clinical practice. Patients receive treatments from researchers of QSYQ or not as they would in the real world, and if they have no preference, the decision for group will be made by researchers according to their professional experience. Patients in the non-exposed group will receive standardized western medication according to patient's clinical conditions, which includes antiplatelet agents, statins, diuretics, angiotensin-converting enzyme inhibitor or angiotensin-receptor blocker, β-blockers, aldosterone receptor antagonist, digoxin, vasodilating agents, and so forth according to HF and chronic stable angina guidelines.^[15,16]^ Patients in the exposure group will be given 1 packet (0.52 g) of QSYQ thrice daily 3 months besides standardized western medication. In both groups, any other Tradiational Chinese Medicine (TCM) drug will be prohibited. Western medicine will be administrated for the comorbidities (such as hypertension or diabetes) and complications according to the relevant guidelines. All drugs will be recorded in case report form.

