### Statistical analysis

2.9

Statistical analysis will be performed by the Clinical Trials Center of First Teaching Hospital of Tianjin University of TCM based on intention-to-treat principle. The continuous variables will be expressed as the mean with standard deviation and tested by *t* tests or Wilcoxon rank sum test. Categorical variables will be expressed as percentages and tested by chi-squared test or Fisher exact test. Survival analysis will be conducted by the log-rank test and Cox regression model. Statistical analysis on the missing data will be adjusted by an estimating equation or statistical model in the final analysis. The statistical significance is defined as *P* <.05. Data analysis will be conducted by Statistical Analysis System (SAS) software version 9.3 (SAS Institute Inc., Cary, NC).

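### The named tests ignore hospital in a non-randomised comparison across 84 hospitals, so the QSYQ effect may be confounded by hospital and the 5% error rate may not hold

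*Protocol article*

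**What the plan says.** Study design (2.1) describes an observational cohort: "A total of 1200 outpatients with IHF from 84 hospitals will in different regions of China are divided into 2 cohorts". Patient preference is the main basis for group membership. Intervention (2.5) adds that, for patients who have no preference, "the decision for group will be made by researchers according to their professional experience".

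Sample size (2.4) assumes that "the rate of cardiac function improvement is 22% of patients in QSYQ group and 15% in control group" and that "The sample size is same in 2 groups". It sets the total at 1200, allowing for 20% dropout, "with a power of 0.8" and two-sided alpha 0.05. No allowance for hospital appears there.

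Statistical analysis (2.9) assigns t or Wilcoxon rank sum tests to continuous variables. For the rest, "Categorical variables will be expressed as percentages and tested by chi-squared test or Fisher exact test". Survival analysis is by log-rank test and Cox regression. An estimating equation or model is mentioned only for missing data. Hospital is not named as a stratum, covariate, random effect or cluster.

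**The concern.** Nothing in the design balances QSYQ use across hospitals. Equal group sizes are an overall assumption and do not imply balance within each hospital. Preferences may differ between regions, and researchers' judgement decides for patients without a preference, so the share of QSYQ users may differ by hospital. Outcomes may differ by hospital too, through case mix, background care or grading habits.

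If both vary, two separate problems follow:

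- **Confounding by hospital.** If hospitals with many QSYQ users tend to have better or worse outcomes for other reasons, part of that difference is credited to QSYQ. This biases the estimate.
- **Understated variance.** Even with no systematic link, chance alignment of hospital outcome levels with hospital QSYQ shares adds variance that a two-sample test does not count, so a nominal 5% test rejects too often.

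The named two-sample tests address neither. At stake is whether a significant NYHA or MLHFQ difference can be attributed to QSYQ rather than to where patients were treated.

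**Working it through.** **Inputs from the article.** 1200 patients, 84 hospitals, improvement rates of 22% and 15%, two-sided alpha 0.05, power 0.80, dropout 20%, equal groups. Evaluable patients: 1200 × 0.8 = 960.

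**Step 1: reproduce the stated sample size.** Two proportions, unpooled variance:

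n per group = (1.96 + 0.84)² × (0.22 × 0.78 + 0.15 × 0.85) / 0.07², which rounds up to 480. Dividing by 0.8 gives 600 per group, 1200 in total.

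The pooled-variance version gives 482 per group, 603 after dropout and 1206 in total. The stated figure is therefore reproduced by a calculation that assumes independent patients.

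**Step 2: patients per hospital.** Enrolled: 1200 / 84 = 14.3. Evaluable: m = 960 / 84 = 11.4.

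**Step 3: variance factor for an exposure set at patient level.**

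DE = 1 + (m − 1) × ICC(outcome) × ICC(exposure)

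True size of a nominal 5% test = 2 × [1 − Φ(1.96 / √DE)]

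The factor exceeds 1 only if both ICCs are positive. The article gives neither, so these are assumptions: outcome ICC 0.01 to 0.10, and four patterns of QSYQ use. Exact balance within hospitals corresponds to an exposure ICC of −1/(m − 1) = −0.096.

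Worked example, outcome ICC 0.10 and exposure ICC 0.3: DE = 1 + 10.43 × 0.10 × 0.3 = 1.313; 1.96 / √1.313 = 1.71; size = 0.087.

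| QSYQ use across hospitals | Exposure ICC | DE (outcome ICC 0.01 to 0.10) | True size |
|---|---|---|---|
| Balanced within every hospital | −0.096 | 0.99 to 0.90 | 0.049 to 0.039 |
| Unrelated to hospital | 0 | 1.00 | 0.050 |
| Moderate clustering | 0.3 | 1.03 to 1.31 | 0.054 to 0.087 |
| Each hospital all-QSYQ or all-control | 1.0 | 1.10 to 2.04 | 0.062 to 0.170 |

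With the effective number of patients reduced to 960/DE, power for 22% versus 15% falls from 0.80 to between 0.79 and 0.68 at exposure ICC 0.3.

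**Step 4: check by simulation.** 84 hospitals of 14 patients, no treatment effect, improvement rate 18.5% (midway between 15% and 22%), outcome ICC 0.05, two-proportion test without hospital, 3000 runs per case:

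| QSYQ use | Simulated size | Formula (m = 14.3) |
|---|---|---|
| Balanced within hospital | 0.044 | 0.044 |
| Unrelated to hospital | 0.046 | 0.050 |
| Exposure ICC 0.3 | 0.081 | 0.074 |
| Exposure ICC 0.5 | 0.089 | 0.090 |
| All-or-none by hospital | 0.121 | 0.129 |

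The two agree well enough to rely on the formula.

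**What the figures leave out.** Both formula and simulation take a hospital's outcome level to be unrelated, on average, to its QSYQ share. A systematic link would add bias on top of these error rates. Its size cannot be derived from the article.

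**The case against.** The strongest objection is that this is a journal article with a one-paragraph statistical section, and that centre terms and variance estimators commonly sit in a full protocol or SAP. That would settle the matter if the article had left the method open. It does not: it names two-sample tests, and a hospital-adjusted primary comparison would depart from them. The Cox model is different, because it can carry a hospital stratum and one may be specified elsewhere. For that model the point is only that none is stated.

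A reader might also draw stronger conclusions, which the documents do not support:

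- **That the P values are certainly too optimistic.** Exposure is set patient by patient. If QSYQ use is unrelated to hospital, the size stays at 5%. If it is balanced within hospitals, the tests are slightly conservative.
- **That the error rate is 17%.** This needs the highest assumed outcome ICC and hospitals with only one exposure group each, which conflicts with choice driven mainly by patient preference.
- **That researchers generally decide who receives QSYQ.** They do so only for patients without a preference.
- **That reported confidence intervals are too narrow.** The statistical section mentions none.
- **That NYHA is rated by local clinicians.** The article does not say who rates it; it says outcome assessors are blinded. Blinding would not remove differences in grading between hospitals, but such differences are a possibility, not a documented fact.

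Finally, stratifying has limits. With 11.4 evaluable patients per hospital and 15% to 22% improving, there are about two improvers per hospital (11.4 × 0.15 = 1.7; 11.4 × 0.22 = 2.5), so some hospitals will contribute little. This affects how the fix is built but does not remove the need for it.

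**Conclusion.** The point holds in conditional form. The named tests do not suit a non-randomised comparison spread over 84 hospitals, because they are safe only if QSYQ use or outcome does not vary by hospital, and nothing in the article supports either condition. If both vary, the estimated effect is confounded by hospital by an amount that cannot be quantified here, and the type I error rises. Under an assumed outcome ICC of 0.01 to 0.10 with 960 evaluable patients, the plausible excess is modest: about 5.4% to 8.7% at an exposure ICC of 0.3. Because the size of the inflation, and whether there is any, depends on two ICCs that are not reported, confidence is moderate. The analysis should be changed; the recruitment target need not be revised on this ground alone.

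**What to change.** In Statistical analysis (2.9), make the primary NYHA and MLHFQ comparisons hospital-stratified or hospital-adjusted. Any of these would serve:

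- a hospital-stratified test, such as van Elteren for ordinal or continuous outcomes or Cochran–Mantel–Haenszel for improvement rates;
- a regression with hospital fixed effects, using a conditional (stratified) form for a binary outcome because there are so few improvers per hospital;
- a model with a random hospital effect that also includes each hospital's QSYQ share. A random intercept alone removes the confounding only partly.

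Stratify the Cox model by hospital or region. Pool very small or single-exposure hospitals by region, under a rule fixed before the data are examined. Cluster-robust standard errors may be added, but they correct the variance only and do not remove confounding by hospital. Reporting the QSYQ share by hospital would show how much the issue matters in practice.

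The cost is a few sentences of analysis wording, with no new data collection, since each patient's hospital is known. The drawbacks are slightly wider intervals and little contribution from single-exposure hospitals unless pooled. Pooling by region leaves any confounding between hospitals within a region.

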**Figure 1 F1:**
[figure not shown]
Flow diagram of study.

### Ethics

2.2

The protocol has been approved by the Ethics Committee of First Teaching Hospital of Tianjin University of traditional Chinese medicine (NO: TYLL2013 [K] 008). It will be conducted in accordance with the Declaration of Helsinki. Written informed consent will be obtained from all participants or their legally authorized representatives when they agree to participate in the study before enrollment.

### Participants

2.3

#### Diagnostic criteria

2.3.1

The patients’ diagnostic criteria are based on European Society of Cardiology guidelines for the diagnosis and treatment of acute and chronic HF 2012 and 2007 Chinese Society of Cardiology guidelines for the diagnosis and treatment for chronic stable angina.^[15,16]^ The definition of IHF refers to HF with the history of coronary heart disease. Patients matching 1 of the following 3 conditions will be diagnosed as coronary heart disease:

(1)with prior or current symptoms, such as dyspnea, fatigue and fluid retention (edema), so on;(2)history of old myocardial infarction with or without percutaneous coronary intervention or/and coronary artery bypass grafting;(3)coronary angiography or coronary Computed Tomography Angiography (CTA) shows stenosis more than 50% in at least 1 of the main coronary arteries with or without revascularization.

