#### Inclusion criteria

2.3.2

(1)Diagnosed with coronary heart disease;(2)Left ventricular ejection fractions (LVEF) ≤50%;(3)New York Heart Association (NYHA) classification II∼IV;(4)Standardized western medicine therapy for IHF currently in a stable condition;(5)Signed informed consent.

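### The one-of-three rule lets heart-failure symptoms alone establish coronary heart disease, so the entry criteria add almost no ischemic requirement and contradict the study's own definition of ischemic heart failure

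*Protocol article*

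**What the plan says.** Section 2.3.1 (Diagnostic criteria) of the protocol article defines the target condition: "The definition of IHF refers to HF with the history of coronary heart disease". It then gives the rule for coronary heart disease: "Patients matching 1 of the following 3 conditions will be diagnosed as coronary heart disease". The three conditions are:

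1. "with prior or current symptoms, such as dyspnea, fatigue and fluid retention (edema), so on"
2. "history of old myocardial infarction with or without percutaneous coronary intervention or/and coronary artery bypass grafting"
3. coronary angiography or CT angiography that "shows stenosis more than 50% in at least 1 of the main coronary arteries with or without revascularization"

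Section 2.3.2 (Inclusion criteria) makes this diagnosis the first entry requirement: "Diagnosed with coronary heart disease". The other requirements are an ejection fraction of at most 50%, NYHA class II to IV, a stable condition on standardized western therapy for IHF, and signed consent. Section 2.3.3 lists eight exclusions. Section 2.3.1 also names a heart-failure guideline and a chronic stable angina guideline as the basis for diagnosis.

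**The concern.** Conditions (2) and (3) are evidence of coronary disease: an old infarction, or a stenosis seen on imaging. Condition (1) is not. Dyspnea, fatigue and edema occur in heart failure of any cause, and the item mentions no angina, infarction, ischemia test or imaging. Because one condition is enough, the weakest of the three sets the rule.

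What is at stake is whom the study is about. The Background rests on the distinction between ischemic and other heart failure, saying that the ischemic form has the worse prognosis, and the aim is stated for IHF. If coronary disease can be inferred from heart-failure symptoms, the two populations become the same on paper and a conclusion specific to IHF loses its footing. The study plans 84 hospitals, and sites can be expected to apply the rule as it is written.

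**Working it through.** **Part 1: the logic of the criteria.** The question is whether any entry criterion requires coronary evidence on its own.

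| Criterion | Place | Requires coronary evidence? |
|---|---|---|
| Coronary heart disease diagnosis | 2.3.2 (1), via 2.3.1 | Only if (2) or (3) is needed. Under the one-of-three rule, (1) is enough |
| Ejection fraction at most 50% | 2.3.2 (2) | No; neutral as to cause |
| NYHA class II to IV | 2.3.2 (3) | No; implies symptoms, so it practically guarantees condition (1) |
| Stable on standardized therapy for IHF | 2.3.2 (4) | Not independently; IHF is defined through the same coronary heart disease rule, so this is circular |
| Consent | 2.3.2 (5) | No |
| Eight exclusions | 2.3.3 | No; none removes heart failure of non-ischemic cause |

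A patient in NYHA class II to IV has current symptoms, so condition (1) is met, coronary heart disease counts as diagnosed and inclusion (1) is satisfied. The definition of IHF, heart failure plus a history of coronary heart disease, then reduces in practice to heart failure with symptoms.

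**Part 2: the plan's own sample size.** Inputs from section 2.4: 22% versus 15% improvement, equal groups, two-sided alpha 0.05, power 0.80, dropout 20%.

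Unpooled formula: n = (1.960 + 0.842)² × (0.22×0.78 + 0.15×0.85) / 0.07² = 7.849 × (0.1716 + 0.1275) / 0.0049 = 479.1, rounded up to 480 per group. With dropout, 480 / 0.8 = 600 per group, 1200 in total. The stated figure is reproduced. The pooled-variance version gives 482 per group and 1206 in total, which is close. The sample size is not in dispute.

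**Part 3: what dilution would do, as illustration only.** Assumptions not found in the documents:

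- a fraction f of enrolled patients is non-ischemic, the same in both groups;
- these patients improve at 15% with or without QSYQ;
- the 22% versus 15% contrast holds in the ischemic patients.

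The exposed-group rate is then p₁ = 0.15 + 0.07 × (1 − f). Power at 480 evaluable per group is Φ[(p₁ − 0.15 − 1.960 × SE₀) / SE₁], where SE₀ is the pooled and SE₁ the unpooled standard error of the difference.

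| f | p₁ | Difference (points) | Power |
|---|---|---|---|
| 0 | 0.220 | 7.0 | 0.80 |
| 0.1 | 0.213 | 6.3 | 0.72 |
| 0.2 | 0.206 | 5.6 | 0.62 |
| 0.3 | 0.199 | 4.9 | 0.52 |
| 0.5 | 0.185 | 3.5 | 0.31 |

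If QSYQ worked equally well in non-ischemic patients, power would be kept, but a claim specific to IHF would still be unsupported.

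**Part 4: power of an analysis confined to patients with coronary evidence.** Under the same assumptions, and if condition (2) or (3) identified exactly the ischemic patients, 480 × (1 − f) per group would remain, at 22% versus 15%:

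- f = 0.2: 384 per group, power about 0.71
- f = 0.3: 336 per group, power about 0.65
- f = 0.5: 240 per group, power about 0.51

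Such an analysis beats the diluted comparison but stays below 0.80.

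**The case against.** **A drafting slip.** Condition (1) reads like the heart-failure half of a two-part definition, or possibly like a condition meant for coronary symptoms, given the stable angina guideline. Either is plausible, but the text says neither. It states that one condition of three is enough, and a general reference to guidelines does not override an explicit rule. Nor is this detail that a condensed article leaves to the full protocol: the article states a rule, and that rule conflicts with its own definition.

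**Any symptomatic patient with a low ejection fraction qualifies.** A reader might infer this, but it goes too far. NYHA class, stable therapy, consent and eight exclusions still apply. What the text supports is narrower: none of them independently demands coronary evidence.

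**Non-ischemic patients are being enrolled, and power is being lost.** The documents do not show this. They give no non-ischemic share, and sites using clinical judgement might admit few such patients. The 22% versus 15% comes from a previous study whose population cannot be seen here. If that population was itself mixed, the 7-point difference is already diluted and Part 3 would count the dilution twice. This part of the objection stands, and the power figures are hypothetical for that reason.

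**Cause of heart failure differs between the groups.** Treatment follows preference, so a reader might infer an imbalance. Nothing in the documents shows that cause is related to the choice of QSYQ, so confounding by cause is not part of this point.

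**Restrict the primary analysis afterwards.** Doing so once patients are enrolled would depart from the intention-to-treat basis in section 2.9 and cost power, as Part 4 shows. That objection also stands, and it argues for a supporting analysis instead.

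**Conclusion.** The point holds as an internal contradiction in eligibility. Read as written, heart-failure symptoms alone establish coronary heart disease. NYHA class II to IV makes that condition nearly universal among candidates, so the coronary requirement adds almost nothing. This conflicts with the section's own definition of IHF and with the study's aim. The conclusion rests only on the wording of sections 2.3.1 to 2.3.3 and needs no assumption about who is actually enrolled.

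The numerical consequence cannot be fixed from the documents. Under the assumptions in Part 3, power would be about 0.72 at a 10% non-ischemic share and 0.31 at 50%, against 0.80 as planned. The total of 1200 reproduces and is not faulted.

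**What to change.** Reconcile sections 2.3.1 and 2.3.2 so that heart-failure symptoms belong to the heart-failure definition and do not by themselves establish coronary heart disease. Coronary evidence, such as the listed conditions (2) or (3), would then have to do so. Add a field to the case report form recording which condition each patient met.

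If enrolment has started, keep the planned analysis set and report a sensitivity or subgroup analysis in patients with documented coronary evidence, stating its lower power. This needs the qualifying condition for patients already enrolled, to be collected from their records where it can be.

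The cost is a short eligibility amendment and one form field. The downside is somewhat slower recruitment.
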